## Background

Cardiac resynchronization therapy (CRT) improves survival, symptoms, and left ventricular (LV) function in patients with medical refractory heart failure and prolonged QRS duration [1–4]. Nevertheless, 30–40% of the patients experience no clinical benefit and the associated risk of complications is non-negligible [5–7].

Potentially correctable causes of non-response to CRT are LV lead positioning and device programming [7, 8]. Guidelines recommend positioning of the LV lead in non-scarred, non-apical, and postero-lateral myocardial segments with late electrical activation [1]. Recent randomized controlled trials have demonstrated improved response to CRT when applying an imaging-guided LV lead placement strategy targeting the latest mechanically activated, non-scarred, myocardial segment, compared with standard care [9–11]. However, imaging-guided strategies are time-consuming, costly, and difficult to align with fluoroscopic imaging during device implantation.

An alternative approach for individualized LV lead placement is to target the myocardial region with the latest electrical activation; a strategy with the advantage of electrical measurements being immediately available during the implant procedure. Retrospective studies have documented an association between pacing the LV in a region with late electrical activation and improved outcome after CRT [12, 13]. However, these studies did not perform systematic electrical activation mapping or evaluate the influence of myocardial scar tissue.

Recently, electrical resynchronization with narrowing of the QRS width during CRT has been associated with better outcome [14]. Furthermore, programming of the interventricular pacing delay (VVd) to achieve the shortest QRS duration is suggested to increase CRT response [15, 16]. Whether the outcome of CRT is improved when combining electrically guided LV lead placement and optimizing the VVd to achieve the shortest QRS duration is unknown.

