### Localization of the myocardial scar

Pre-implant ECG-gated Rb-PET is performed in all patients using a commercially available scanner (GE Healthcare, Buckinghamshire, UK). Briefly, intravenous injection of 1150 MBq rubidium is directly followed by a 7-min list mode scan of the heart. List mode data are subsequently re-binned into 27 dynamic frames (12 × 5, 6 × 10, 4 × 20, 4 × 40, and 1 × 60 s) and one static frame (2.5–7 min following initiation of the scan). Resting MP values are calculated from dynamic Rb PET/CT images and normalized for differences in rate pressure product (RPP) using an assumed population average value of 10,000 divided by the RPP. Data are analyzed using the commercially available automatic program Quantitative PET (Cedar-Sinai Medical Center, Los Angeles, CA, USA). Static data are displayed in polar map format and analyzed using the 17-segment model (Fig. 3d) [24]. Segments with a tracer uptake < 50% are considered as transmural scar tissue, those between 50 and 75% as non-transmural scar tissue, and those ≥ 75% are considered viable myocardium [26].

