### Sample size

We hypothesize that the intervention group strategy will result in an excess increase in LVEF of 4% compared with the strategy used in the control group, where an 8% increase in LVEF is expected [9]. To identify this absolute increase in LVEF of 12% in the intervention group and to achieve statistical power of 80%, the study will need a sample size of 98 patients, given a standard deviation (SD) of 7% in both groups, and a two-sided alpha value of 0.05. To achieve statistical power of 80% for the secondary endpoint of relative reduction in LVESV a sample size of 116 patients is needed, when assuming a 33% reduction in the control group and a 45% reduction in the intervention group (expected SD of 23% in both groups and given a two-sided alpha value of 0.05%). To achieve statistical power of > 80% with a margin of non-inferiority of 20% for the secondary endpoint of clinical response to CRT (assuming a 75% clinical response rate in the control group) we will need a sample size of 116 patients (given a two-sided alpha value of 0.05%). Taking into consideration expected loss to follow up in approximately 5% of patients, 122 patients are included.

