### Statistical analysis

All analyses will be conducted according to the intention-to-treat principle and will be performed before breaking the randomization code. Baseline characteristics are presented and compared clinically. Primary and secondary endpoints will be analyzed using linear regression for continuous variables and logistic regression for binary outcome measures, including heart failure etiology as a variable in the model. Multivariate regression analysis will be reported for absolute change in LVEF including baseline LVEF, heart failure etiology, sex, and baseline QRS width as covariates. Predictors of missing outcome values will be identified by comparing baseline characteristics and will be included in a multivariate regression model for sensitivity analysis. Intraclass correlation coefficients are computed to assess intraobserver and interobserver agreement for the echocardiographic parameters included in the primary endpoint: LVEF, LVEDV, LVESV assessed for 20 echocardiograms. A two-sided *P* value < 0.05 is considered significant.

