### Methods used in the ElectroCRT study

The extent of myocardial scar tissue is inversely related to the response to CRT [31] and placement of the LV lead in a myocardial region with scar tissue is associated with poor CRT outcome [32]. Rb-PET is well-established for visualizing regions [26, 33] and distribution of myocardial scar [34], but it has lower spatial resolution than cardiac magnetic resonance (MR). However, we chose to assess scar with MP imaging, as a substantial proportion of our patients are not eligible for cardiac MR due to an indwelling device. Myocardial scar as detected by MP imaging is not considered in the electrically guided intervention group when implanting the LV lead, to ensure complete separation of the electrically and imaging-guided strategy.

Pre-implant cardiac CT is applied to assess CS anatomy as potentially available CS tributaries may be missed during fluoroscopic balloon occlusive angiography and to ease planning implantation of the LV lead. Post-implant cardiac CT is performed to determine the final LV pacing site because fluoroscopy has been shown to be inaccurate and poorly reproducible for this purpose [35].

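### Baseline scar extent, measured in every patient before randomization and described as related to CRT response, is not among the named covariates for change in LVEF: a modest forgone gain in precision, not an error

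*Protocol article*

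**What the plan says.** The Statistical analysis section of the protocol article describes two regressions that bear on LVEF. Primary and secondary endpoints are analysed by linear or logistic regression with heart failure etiology in the model. A further model is then announced: "Multivariate regression analysis will be reported for absolute change in LVEF including baseline LVEF, heart failure etiology, sex, and baseline QRS width as covariates". Neither contains a scar term, and no outcome in the Endpoints section names scar. The nearest outcome there concerns dyssynchrony, LV lead placement and response.

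Elsewhere the article says three things about scar:

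- **It is measured in everyone.** Under Localization of the myocardial scar: "Pre-implant ECG-gated Rb-PET is performed in all patients using a commercially available scanner". Each of 17 segments is classed by tracer uptake, with uptake below 50% counted as transmural scar. The Randomization section places allocation after pre-implant imaging.
- **It is described as prognostic.** Under Methods used in the ElectroCRT study: "The extent of myocardial scar tissue is inversely related to the response to CRT".
- **The arms handle it differently.** In the control arm the lead is aimed at non-scarred segments. For the other arm: "Myocardial scar as detected by MP imaging is not considered in the electrically guided intervention group when implanting the LV lead". The stated reason is to keep the two strategies separate.

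**The concern.** A covariate is worth adjusting for when it is measured before randomization, is observed in nearly everyone and is believed to predict the outcome. On the article's own account scar extent meets all three conditions. The article also does not leave covariates to a later document: it names four, and scar is not one of them. Etiology (ischemic or not) is included, but a two-level factor can carry only part of the information in a 17-segment count.

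What is at stake is the width of the confidence interval for the LVEF difference. There is also a smaller descriptive matter. Since the two strategies differ by design in how they treat scar, a reader of the results will want to know how often the lead ended up in scar in each arm. The article names no summary that would show this.

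**Working it through.** **Inputs from the protocol (Sample size; Study design).** Difference 4 LVEF points (12 against 8), SD 7 in both groups, two-sided alpha 0.05, power 80%, allocation 1:1, 122 enrolled, about 5% loss.

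**Assumed input.** r, the partial correlation of scar extent with LVEF change beyond the other covariates in the model. The documents do not give it. The range used is 0 to 0.4.

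**Step 1: the plan's own figure.** Per arm, n = 2(1.960 + 0.842)² × 7² / 4² = 48.1, rounded up to 49, so 98 in total. The stated figure reproduces, and it assumes no gain from covariates.

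**Step 2: patients available.** 122 × 0.95 = 115.9, or about 116, which is 58 per arm.

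**Step 3: power without scar.** SE = 7 × √(2/58) = 1.300. The 95% half-width is 1.96 × 1.300 = 2.55 points. Noncentrality is 4/1.300 = 3.08 on 114 degrees of freedom, and noncentral-t power is 86.2%. The normal approximation gives 86.8%.

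**Step 4: power with scar.** Take 7 as the residual SD before scar enters. After adjustment the SD is 7√(1 − r²). The equivalent gain in sample size is 1/(1 − r²) − 1.

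| r | SD | SE | 95% half-width | Power | Equivalent extra patients |
|---|---|---|---|---|---|
| 0 | 7.00 | 1.300 | 2.55 | 86.2% | 0% |
| 0.2 | 6.86 | 1.274 | 2.50 | 87.6% | 4% |
| 0.3 | 6.68 | 1.240 | 2.43 | 89.2% | 10% |
| 0.4 | 6.42 | 1.191 | 2.34 | 91.5% | 19% |

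A simulation of 3,000 runs, with scar correlated with etiology and etiology in both models, agrees within simulation error. Power went from 0.861 to 0.878 at r = 0.21, from 0.857 to 0.881 at r = 0.30 and from 0.865 to 0.918 at r = 0.41. At r = 0 it went from 0.858 to 0.855, so the cost of an uninformative covariate is negligible. The simulation did not include baseline LVEF, sex or QRS width. If scar overlaps with those, the relevant r in the four-covariate model is smaller.

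**Step 5: precision of an arm-by-scar term.** If scar were split 50:50, each of four cells would hold 116/4 = 29 patients. The SE of the interaction is 7 × √(4/29) = 2.60 and the 95% half-width 1.96 × 2.60 = 5.1 points. With scar kept continuous, the SE per SD of scar extent is about 2 × 7/√116 = 1.30, a half-width of 2.55 points per SD, or again 5.1 over a contrast of two SDs. Set against a target effect of 4 points, this can only be exploratory.

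**The case against.** The strongest reply is that nothing here is wrong. Randomization makes the comparison unbiased whether or not scar is adjusted for. The sample size reproduces without it, and expected power is already above the 80% target. Etiology, a related factor, is both a stratification factor and a covariate. The article does not call its list exhaustive, and a full protocol or analysis plan that is not shown may say more, especially on exploratory analyses. All of this stands, and it is why the point is rated low.

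A second objection also stands. The four-covariate model appears to be additional to the etiology-adjusted model that is described for the primary endpoint. Adding scar only to the former would leave the primary interval as it is.

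Three stronger readings are tempting, and the documents do not support them.

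- A reader might infer that the trial leaves open a question that it set itself. The Background does say of earlier retrospective work that "these studies did not perform systematic electrical activation mapping or evaluate the influence of myocardial scar tissue". But that describes a limitation of those studies. The aim stated at the end of the Background is confined to the LVEF comparison of the two strategies.
- A reader might infer that the scan is wasted in the electrical arm. It has to be done before allocation is known, it keeps the work-up identical, and it guides placement in the control arm.
- A reader might suppose that the electrical strategy works only in patients without scar, so that the pooled effect is diluted. The documents give neither subgroup effects nor the share of patients with scar, and a covariate would not cure effect modification in any case.

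**Conclusion.** The point holds as a low-severity improvement. The protocol names its covariates for LVEF change and leaves out one that it measures in everyone before randomization and itself describes as related to response. The comparison is not biased and the sample size is unaffected. The forgone gain is about 1 to 5 points of power (86.2% to between 87.6% and 91.5%) and at most about 0.2 points off the confidence-interval half-width (2.55 to 2.34), for r between 0.2 and 0.4. It is nil at r = 0. These figures assume 58 evaluable patients per arm, a residual SD of 7 before scar is added, and an r that the documents do not supply. Overlap with etiology and the other named covariates would place the gain towards the lower end.

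**What to change.** Before the randomization code is broken, add one sentence to the Statistical analysis section. It should name baseline Rb-PET scar extent, defined as the number of the 17 segments with tracer uptake below 50% and entered as a continuous variable, as a covariate in the multivariable model for LVEF change. If the primary confidence interval is to benefit, include it in the etiology-adjusted primary model as well and say so there.

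As clearly labelled exploratory items, report:

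- the arm-by-scar-extent term with its confidence interval, noting the expected imprecision of about ±5 points;
- by arm, the share of CT-located final pacing sites lying in a segment with uptake below 50%, among patients who have a post-implant CT (the protocol exempts some from CT, for example those with reduced renal function).

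The cost is one degree of freedom in about 116 patients, some overlap with etiology, and no new data. The timing matters: the same covariate added after unblinding would look post hoc.

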## Discussion

### Electrically guided CRT strategy

Positioning of the LV lead according to the latest activated myocardial segment has been shown to be an important determinant of response to CRT. In this current study, the strategy is to target the myocardial region with the latest electrical activation. The advantage of this approach is that the electrical data obtained from mapping are readily available during the implant procedure without the need for alignment of imaging modalities to target a specific myocardial segment. Several observational studies indicate that a LV lead location in regions with late electrical activation is associated with improved clinical outcome and reverse remodeling [12, 13, 28]. No randomized studies have evaluated the impact of systematic electrical mapping of available CS branches to target the segment with the latest electrical activation. In addition, post-implant device programming in the VVd producing the shortest biventricular paced QRS duration will be applied to optimize the electrical resynchronization suggested to increase the response to CRT [16]. The impact of this combined electrical CRT optimization strategy has not previously been evaluated.

### Imaging-guided LV lead placement

Randomized studies have demonstrated that targeting LV lead placement towards the latest mechanically activated non-scarred myocardial area as assessed by speckle-tracking echocardiography strain analysis improves clinical outcome and LV reverse remodeling compared with a routine anatomical approach targeting the non-apical posterolateral region [9, 11]. Similar findings have been observed using a multimodality imaging-guided approach combining speckle-tracking echocardiography, MP imaging, and cardiac CT to target the cardiac vein closest to the latest contracting non-scarred myocardial region [10, 17]. However, echocardiographic measurement of the myocardial mechanical activation pattern may be difficult to align with fluoroscopic imaging during the implant procedure [29] and may have substantial degree of interobserver variability [30]. Furthermore, pre-implant imaging is costly and time consuming.

Due to the superior outcome associated with the imaging-guided approach as compared with conventional LV lead placement [9–11], we applied the imaging-guided approach as our control group strategy. This was done to evaluate the potential benefit of the simpler electrically guided CRT optimization strategy not limited by the need for pre-implant imaging and alignment of imaging modalities.

### Methods used in the ElectroCRT study

The extent of myocardial scar tissue is inversely related to the response to CRT [31] and placement of the LV lead in a myocardial region with scar tissue is associated with poor CRT outcome [32]. Rb-PET is well-established for visualizing regions [26, 33] and distribution of myocardial scar [34], but it has lower spatial resolution than cardiac magnetic resonance (MR). However, we chose to assess scar with MP imaging, as a substantial proportion of our patients are not eligible for cardiac MR due to an indwelling device. Myocardial scar as detected by MP imaging is not considered in the electrically guided intervention group when implanting the LV lead, to ensure complete separation of the electrically and imaging-guided strategy.

Pre-implant cardiac CT is applied to assess CS anatomy as potentially available CS tributaries may be missed during fluoroscopic balloon occlusive angiography and to ease planning implantation of the LV lead. Post-implant cardiac CT is performed to determine the final LV pacing site because fluoroscopy has been shown to be inaccurate and poorly reproducible for this purpose [35].

### Choice of endpoint

Considering the complex design, this trial would be difficult to conduct as a multi-center study, and therefore it does not have statistical power to investigate differences between groups in “harder” endpoints such as survival or hospitalization due to heart failure. We chose LVEF as the primary endpoint, because it is a commonly used and universally understood echocardiographic measure of LV systolic function, which furthermore is a good predictor of survival in patients with CRT [36]. Accordingly, the findings in this study may generate hypotheses to be tested in future larger-scale, multi-center, randomized studies.

### Limitations of the ElectroCRT study

We acknowledge the inherent limitations of a single-center study design. Nevertheless, the double-blinded, randomized, controlled trial design for comparing two advanced strategies for CRT optimization is the strongest research instrument to investigate a difference in outcome caused by these interventions.

We do not merge the applied imaging modalities and the procedural fluoroscopy in the control group. However, we use the standard myocardial segmentation [24] to ease an approximated alignment of the echocardiography, MP imaging, 2D and 3D cardiac CT reconstructions of cardiac venous anatomy and procedural fluoroscopy [10].

The introduction of cardiac CT and Rb-PET prior to CRT will increase the patient’s cumulative radiation exposure. Several approaches to minimize radiation dose are applied in this study, including the use of iterative reconstruction algorithms, application of prospectively triggered high-pitch CT scans, individual settings of tube voltage and current, and the use of Rb-PET for MP imaging, respectively. Furthermore, the utility and potential benefits of participating in this study are expected to equalize the risks of exposure to ionizing radiation, possible adverse effects, and inconvenience to the patients.

### Perspective

No randomized trial has investigated the effect of a CRT implant-strategy targeting optimal electrical resynchronization achieved by guiding LV lead placement to the myocardial region with the latest electrical activation combined with post-implant VVd optimization for narrowing the paced QRS width. If an excess increase in LVEF is achieved by LV lead implantation guided by systematic electrical mapping followed by VVd optimization for narrowing paced QRS, this study supports the conduct of larger, multicenter, randomized clinical trials investigating the impact of electrically guided LV lead implantation on clinical outcomes in patients treated with CRT.

## Trial status

Patients were enrolled between 16 February 2015 and 13 December 2017. The current protocol article was submitted to *Trials* before all patients were enrolled and before analyzing any data and breaking the randomization code.

## Abbreviations

2D: Two-dimensional
3D: Three-dimensional
6MFU: Six-month follow-up
6MWT: Six-minute walk test
AIV: Anterior interventricular vein
Ant: Anterior
Ant-Sept: Antero-septal
AV: Atrioventricular
CABG: Coronary artery bypass Graft
CRF: Case record form
CRT: Cardiac resynchronization therapy
CRT-D: Cardiac resynchronization therapy defibrillator
CRT-P: Cardiac resynchronization therapy pacemaker
CS: Coronary sinus
CT: Computed tomography
ECG: Electrocardiogram
eGFR: Estimated glomerular filtration Rate
EGM: Electrogram
Inf: Inferior
LAD: Left anterior descending artery
Lat: Lateral
LBBB: Left bundle branch block
LMA: Left marginal artery (circumflex artery branch)
LMV: Left marginal vein
LVEDV: Left ventricular end-diastolic volume
LVEF: Left ventricular ejection fraction
LVESV: Left ventricular end-systolic volume
MBq: Mega Becquerel
MCV: Middle cardiac vein
mHz: Megahertz
ml: Milliliters
MLHFQ: Minnesota Living with Heart Failure Questionnaire
MP: Myocardial perfusion
MR: Magnetic resonance
ms: Milliseconds
Nt Pro-BNP: N-terminal prohormone of brain natriuretic peptide
NYHA: New York Heart Association
OMT: Optimal medical treatment
PDA: Posterior descending artery (right coronary artery branch)
PLA: Posterolateral artery
Post: Posterior
PV: Posterior vein
QLV interval: The interval from onset of the QRS on the surface 12-lead ECG to the maximum voltage change over time recorded in the EGM, reflecting the near-field activation of the myocardium according to the LV lead
QoL: Quality of life
Rb-PET: ^82^Rubidium positron emission tomography
RCA: Right coronary artery
RV: Right ventricle/right ventricular
SAX: Short axis view
Sept: Septal
SPIRIT: Standard Protocol Items: Recommendation For Interventional Trials
TDI: Tissue Doppler Images
VVd: Interventricular pacing delay
